## Abstract

Atopic dermatitis (AD) is a relapsing and remitting chronic inflammatory skin disease for which a variety of etiological factors are involved. Treatment strategies should be multifaceted and have few side effects. In this respect, acupuncture has become increasingly popular as a safe, consistently effective, and drug-free therapy that treats multiple AD symptoms. We aim to not only verify the effectiveness of acupuncture but also suggest patient-specific response determinants and a new underlying mechanism implicating the gut-brain axis. We have designed a randomized, participant-blinded, sham-controlled clinical trial for 60 mild to moderate AD patients. In a previous study, we observed that the clinical skin symptoms of AD were closely associated with gastrointestinal (GI) symptoms. From these findings, we developed an intervention with six acupuncture points: three for AD symptoms and three for GI symptoms. Also, since high responders and low responders to the acupuncture treatment could be identified in the previous study, we now aim to explore response-determining factors, with a particular focus on GI symptoms. Therefore, we will precisely evaluate not only AD symptoms using the SCORAD, EASI, and DLQI tools, but also GI symptoms using the GSRS, TDS, BSFS, and AR tools and abdominal examination. AD develops in association with complicated pathophysiological factors, such as skin barrier function, genetic susceptibility, and immunological factors. Moreover, the underlying mechanism by which acupuncture treatment works has not been clearly elucidated. We, therefore, will conduct a simultaneous cross-sectional study with a sample of 40 healthy individuals, wherein potential indicators, such as fMRI, gut microbiota, and serum TARC and ATX, will be investigated to determine the gut-brain axis-associated mechanism of acupuncture. We expect that the results of this study could provide important clinical evidence for the effects of acupuncture and help elucidate the therapeutic mechanisms that underlie acupuncture's efficacy in AD treatment. This trial is registered with https://clinicaltrials.gov/ct2/show/KCT0005422 (Trial registration: Korean Clinical Trial Registry (http://cris.nih.go.kr; registration number: KCT0005422); date of registration: September 23, 2020).

## 1. Introduction

Atopic dermatitis (AD) is a relapsing and remitting, inflammatory, chronic skin disease that is characterized by severe itching and eczema [1]. Its prevalence varies widely according to geographic location, but according to an International Study of Asthma and Allergies in Childhood (ISAAC)-based report, it is on the rise worldwide, with a global prevalence of approximately 230 million [1, 2]. Additionally, the factors involved in AD pathophysiology are complex and diverse, and recent focus has mainly been on the hygiene hypothesis, loss-of-function mutations of the FLG-encoding gene, environmental factors, and the gut microbiota-skin axis [3].

However, AD cannot be cured [3]. Therefore, multistep guidelines have been outlined to control symptoms and maintain remission for as long as possible. However, in clinical practice, many patients do not respond properly to existing treatments. Persistent, recurring skin symptoms also exist because of treatment discontinuity. On the other hand, if continuous systemic treatment is administered, concerns about side effects and complications come to the forefront [4]. Therefore, to cope with the limitations of these existing treatments, the potential role of East Asian medicine, including Korean medicine, is being actively studied [5, 6]. A recent paper reported that acupuncture is a safe AD treatment that can be effective at improving itchiness, Eczema Area and Severity Index (EASI) scores, and other global symptoms [6].

Our research team has conducted previous randomized controlled trials (RCTs) addressing AD-related topics [7, 8]. Thirty-eight patients with AD were recruited, divided into two groups, and treated with verum or sham acupuncture twice a week for 4 weeks. In that study, acupuncture was performed on three fixed acupoints (ST36, LI11, and PC6 bilaterally) and two additional points. Additional points were selected on an individualized basis according to the accompanying symptoms, such as ST43 and GB41 for gastric stiffness and tenderness or LI2 and GB31 for diarrhea and constipation. Through this study, we not only confirmed the effectiveness of acupuncture treatment but also highlighted two notable implications. The first was that AD severity and the presence of gastrointestinal (GI) symptoms were positively correlated, and the second was that some patients exhibited clear improvements, but some patients did not.

Based on these two implications, the main purpose of this study is to explore the response determinants of acupuncture treatment. We plan to explore the underlying mechanisms simultaneously. Based on the gut-brain axis theory [9], we will analyze gut microbiota composition using fecal samples, and we will analyze brain activity and connectivity data using functional magnetic resonance imaging (fMRI). As links between fMRI and gut microbiota data, we will also collect serum thymus and activation-regulated chemokine (TARC) levels and autotaxin (ATX) levels.

## 2. Methods

### 2.1. Objectives

The primary purpose of the present study is (1) to determine the response determinants of acupuncture treatment and (2) explore the underlying mechanism of acupuncture, mainly focusing on the gut-brain axis.

### 2.2. Trial Design and Setting

This study will combine an RCT and a cross-sectional component, as summarized by the study flowchart (Figure 1).

#### 2.2.1. Randomized Controlled Trial

The RCT component will include only 60 participants with mild to moderate AD. Forty and twenty participants will be randomly assigned to the verum acupuncture (VA) group and sham acupuncture (SA) groups, respectively. It will be a randomized, assessor- and participant-blinded, sham-controlled trial with a parallel-group design. All trial processes and procedures will be carried out at the Kyung Hee University Korean Medicine Hospital and Korea University Brain Imaging Center (KUBIC) in Seoul, Korea.

#### 2.2.2. Cross-Sectional Component

The cross-sectional component will include 40 healthy controls and 60 patients with AD. The study will be conducted at the Kyung Hee University Korean Medicine Hospital and KUBIC.

#### 2.2.3. Sample Size Calculation

This is not a confirmative study to evaluate the effectiveness of acupuncture. In our previous study [8], we have already confirmed the effectiveness of acupuncture treatment on patients with mild to moderate AD. The aim of this study is to discover the response determinants and the mechanism of action of acupuncture treatment for AD, mainly focusing on the gut-brain axis. Therefore, to calculate the sample size of this study, we considered a sample size of 18 per group calculated based on the SCORAD (total) score as the primary endpoint in our previous study [8] and a sample size of 12 in another study that had a similar design and explored treatment response determinants [10] as well as allocation of the verum acupuncture (VA) and sham acupuncture (SA) groups at a ratio of 2 : 1 to examine the difference in treatment response according to GI symptoms in the acupuncture treatment group. Considering the aim of the present study and the sample size of these previous studies, under the expert agreement, we calculated the required sample sizes for the AD VA, AD SA, and healthy control groups as 40, 20, and 40, respectively.

### 2.3. Ethics and Dissemination

The institutional review board (IRB) of Kyung Hee University Korean Medicine Hospital approved this study on July 21, 2020 (IRB No: KOMCIRB 2020-06-003). This study was registered in the Korean Clinical Trial Registry (CRIS, registration number: KCT0005422). All information regarding the study protocol will be provided to each participant. Written informed consent will also be obtained.

### 2.4. Eligibility Criteria

#### 2.4.1. Inclusion Criteria

*(1) Healthy Group*
Men and women aged 19 to 49 years able to read and write the Korean languageBody mass index (BMI) of 18.5 or more and less than 25 (kg/m^2^)Right-handedDo not have AD diagnosed in accordance with the Hanifin and Rajka criteria [11].Agreement with the study protocol and providing written informed consent

*(2) AD Patient Group*
Men and women aged 19 to 49 years able to read and write the Korean languageBody mass index (BMI) of 18.5 or more and less than 25 (kg/m^2^)Right-handedAD diagnosed in accordance with the Hanifin and Rajka criteria [11].Scores from 10 to 40 points of the objective Scoring Atopic Dermatitis (SCORAD) scaleAgreement with the study protocol and providing written informed consentDo not participate in other clinical studies in the preceding month

#### 2.4.2. Exclusion Criteria

Those who have taken drugs (especially antibiotics), within 1 month before study participation that have the potential to affect the study resultsThose who have taken functional foods for health (especially probiotics and prebiotics) within 1 month before study participation, which have the potential to affect the study resultsThose who have a history of alcohol consumption within 1 week before study participationThose with extensive tattoos or (semi-)permanent facial makeupThose with claustrophobiaThose who cannot lie down for a certain amount of time due to pain or discomfortThose with nonremovable implanted metal devices, such as pacemakers, clips, and implantations.(For women) Those who are pregnant or breastfeeding(For women) Those with intrauterine contraceptivesThose who have had eye surgery (excluding LASIK and LASEK)Those who have been diagnosed with other diseases (neuropsychiatric disorders, brain surgery history, stroke, epilepsy, dementia, alcohol or drug use disorder, etc.) that may affect the results.Those who have been diagnosed with somatosensory-related diseases (Raynaud's disease, chronic pain disease, etc.)SmokersThose who are adjudged to be unsuitable participants of this study based on physical or mental incompatibilities

### 2.5. Participant Recruitment

We will recruit 60 patients with AD and 40 healthy controls. Recruitment will mainly proceed via bulletin board posts in the hospital. We plan to also postannouncements in nearby town offices and campuses.

### 2.6. Randomization and Allocation Concealment

Participants who meet the criteria and sign a consent form will be randomly assigned. Block randomization will be conducted to form the verum acupuncture (VA) and sham acupuncture (SA) groups at a ratio of 2 : 1, and the specific randomization method will proceed as follows.

An independent statistical expert will generate a random number table using random allocation software (SAS 9.2 (PROC PLAN, SAS Institute Inc., Cary, NC, USA)). This random number table will be sent to administrative staff at the Acupuncture and Meridian Science Research Center (AMSRC), who are not involved in assessing or recruiting the participants. The staff will place each random number in a sealed, opaque envelope and store them. After the screening, the investigator will contact the administrative staff by e-mail or phone, and the personnel will immediately forward a document that contains the group allocation and participant's unique random number. The investigator will keep this e-mail in the trial master file in printed form.

There will be no randomization of the 40 healthy controls. Only 25 of them can volunteer for fMRI Task 2, which will be conducted on a first-come, first-served basis.

### 2.7. Blinding and Code-Breaking

In the AD group, the participants will be blinded. During the acupuncture sessions, a screen will be erected so that the participants cannot see the Korean medical doctor (KMD) who applies the acupuncture treatment. However, due to the characteristics of acupuncture intervention, it is impossible to blind the acupuncture practitioner. However, the KMD administering acupuncture will not participate in data collection, analysis, and evaluation of results; these functions will be applied by blinded investigators. If serious adverse reactions occur or the participant asks to pause or terminate the session, the acupuncture treatment will be immediately stopped, and the blinding code will be broken.

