### 2.11. Outcome Measures

The study outcomes will be evaluated by an investigator blinded to the treatment assignments. There will be no separation between primary and secondary outcomes since the aim of this study is not to confirm the effectiveness of acupuncture treatment in patients with AD but to discover the response determinants and the mechanism of action of acupuncture treatment for AD, mainly focusing on the gut-brain axis.

Clinical outcomes can be divided into three categories: First, we will assess (1) symptoms of AD (changes in SCARAD, EASI, and Dermatology Life Quality Index [DLQI] assessments). We will also assess (2) GI symptoms (changes in abdominal examination findings, as well as changes in scores according to the Gastrointestinal Symptom Rating Scale (GSRS), Total Dyspepsia Symptom (TDS) scale, Bristol Stool Form Scale (BSFS), and the adequate relief of functional dyspepsia pain and discomfort (AR) assessment). These values will be measured at week 0 (baseline), week 2 (midterm), and week 4 (endpoint).

Finally, since this study aims to explore the mechanism of acupuncture, we will also investigate (3) gut-brain axis indicators. First, the changes in the intensity of blood-oxygen level-dependent (BOLD) signals in the pain and itch matrix, including the thalamus, insula, and cingulate cortex, will be measured using fMRI. Additionally, the functional connectivity between the pain and itch matrix regions will be analyzed. Second, a fecal sample will be taken, and the composition of the gut microbiota in the feces will be analyzed. Blood samples will also be collected and analyzed for TARC and ATX in the serum.

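### Breaking the blinding code whenever a participant asks to pause or end a session needlessly puts participant and assessor blinding at risk

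*Protocol article*

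**What the plan says.** Section 2.2.1 describes the randomised part as blinded for both assessors and participants, with 40 patients on verum acupuncture (VA) and 20 on sham (SA). Section 2.11 adds: "The study outcomes will be evaluated by an investigator blinded to the treatment assignments". Section 2.7 accepts that the practitioner cannot be blinded and so keeps that person away from the data: "the KMD administering acupuncture will not participate in data collection, analysis, and evaluation of results; these functions will be applied by blinded investigators".

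Section 2.7 then sets the code-break rule. A serious adverse reaction is one trigger. The other is that "the participant asks to pause or terminate the session, the acupuncture treatment will be immediately stopped, and the blinding code will be broken". All these events lead to the same consequence. The sentence does not require that the allocation be needed for anything, and it does not say who learns it.

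On a related matter, section 2.6 has the allocation requested after screening: "the investigator will contact the administrative staff by e-mail or phone". In reply, "the personnel will immediately forward a document that contains the group allocation and participant's unique random number". Then: "The investigator will keep this e-mail in the trial master file in printed form". The administrative staff are described as people "who are not involved in assessing or recruiting the participants". No such statement is made about the investigator who receives the e-mail.

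**The concern.** Codes are normally broken because someone who does not know the allocation has to know it. Here the person at the bedside already knows it, so a break at a pause tells that person nothing. It can only pass the allocation to someone who was blinded: the participant, an assessor or other study staff.

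Most of the clinical outcomes depend on what the participant reports or what an assessor judges. DLQI, GSRS, TDS, BSFS and AR come from the participant, and SCORAD includes itch and sleep as subjective items (section 2.11.1). In a sham-controlled trial, a participant who learns which needle was used may answer these differently. If requests were more common in one arm, unblinding would be unbalanced, and the VA-versus-SA comparison of these outcomes in section 2.12.1 could be biased.

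**Working it through.** The documents give no figure for blinding, code-breaks or pause requests, so there is nothing to reproduce. The check is mainly a comparison of the text.

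**Step 1: whom can the break inform?** The practitioner is unblinded by design (section 2.7). Anyone newly informed must therefore be someone blinded. Section 2.7 neither names the recipient nor keeps the assessor out.

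**Step 2: does the participant still provide data afterwards?** Table 1 schedules SCORAD, EASI, DLQI, GSRS, TDS and the stool scale at baseline, mid-treatment and the final assessment, and AR from the second session onwards. Someone who only paused and continued would complete the remaining assessments after the break. Section 2.10 keeps participants who drop out before the sixth session in the analysis with last-visit data. That visit may come before the break, and the text does not settle this.

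**Step 3: is imbalance by arm plausible?** VA uses 9 needles (3 bilateral points and 3 unilateral, 3 × 2 + 3 = 9), inserted 5 to 30 mm and rotated by hand to seek de qi (section 2.9 and Table 3). SA uses a non-penetrating device at 3 bilateral sites (3 × 2 = 6). More requests in VA are plausible, but no rate is documented for either arm.

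**Step 4: illustration of size.** Inputs from the documents: 8 sessions (Table 3), 60 participants, 40 VA and 20 SA (section 2.2.1). Assumed input: probability *p* of a pause or stop request per session, with sessions independent. The chance of at least one request is 1 − (1 − *p*)^8.

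| Assumed *p* per session | 1 − (1 − *p*)^8 | Of 60 | Of 40 VA | Of 20 SA |
|---|---|---|---|---|
| 0.5% | 3.9% | 2.4 | 1.6 | 0.8 |
| 1% | 7.7% | 4.6 | 3.1 | 1.5 |
| 2% | 14.9% | 9.0 | 6.0 | 3.0 |
| 5% | 33.7% | 20.2 | 13.5 | 6.7 |

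If the rates differed by arm, say 2% in VA and 0.5% in SA (again assumed), about 6.0 of 40 VA codes and 0.8 of 20 SA codes would be broken. If requests cluster in a few people, the same average rate unblinds fewer participants, so the table gives upper values for each assumed rate.

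**Step 5: the allocation e-mail.** Sections 2.7 and 2.11 use *investigator* for the blinded rater, and section 2.6 uses it for the holder of the allocation record. The article does not say whether they are the same person, or who can open the master file.

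**The case against.** A reader might infer that these rules undo assessor blinding altogether. The documents do not support that. Section 2.7 does not say the assessor is told at a code-break, and the participant is at least as direct a recipient. The rule affects only those who ask. Sections 2.7 and 2.11 assign rating to blinded investigators, and section 2.12 keeps the statisticians independent and blinded.

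A reader might also infer from section 2.6 that the rater receives every allocation, so that all 60 could be known. That does not follow either. Someone must receive the allocation for treatment to start, and a separate unblinded investigator would satisfy sections 2.6, 2.7 and 2.11 together. Filing the e-mail unblinds assessors only if they can open the file, which is not stated. Delegation of roles and file access are details an article may leave to the full protocol or the operating procedures mentioned in section 2.15.

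The size is assumed, and the excess in VA is not documented. The consequence is also limited. The trial is not meant to confirm effectiveness (section 2.2.3). The response-determinant regression in section 2.12.1 is run within the VA group, so a difference in unblinding between arms does not bias it in the way it could bias a VA-versus-SA comparison. Microbiota, TARC and ATX are laboratory measures. If a request ended participation, there might be few or no ratings after the break.

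All of this stands, and it reduces the point from blinding undone to blinding put at risk. It does not remove the point. The pause trigger is a stated rule, not a detail left out, and as written it gives up blinding with no stated need.

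**Conclusion.** The concern holds in a limited form. As written, section 2.7 breaks the code on a mere request to pause or terminate a session. Because the practitioner already knows the allocation, the only possible effect is to inform someone who was blinded. This puts at risk the participant and assessor blinding promised in sections 2.2.1, 2.7 and 2.11, chiefly for participant-reported and rated outcomes collected after the break in people who continue.

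The size is unknown. The range of about 8% to 34% of participants rests wholly on an assumed 1% to 5% request rate per session and on independence across 8 sessions. An excess in VA is plausible but not documented. The shared use of *investigator* in sections 2.6, 2.7 and 2.11 is an ambiguity to clear up, not a contradiction.

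**What to change.** 1. Reconcile the code-break sentence in section 2.7 with the blinding statements in sections 2.2.1, 2.7 and 2.11, so that a request to pause or stop does not by itself break the code. Leave the rule on when treatment is stopped unchanged.
2. State who is told at any code-break, and that outcome assessors are not told.
3. Log each unblinding with its date and reason, and report the numbers by arm. Any analysis that leaves out unblinded participants should be a sensitivity analysis only, with the caveat that it selects on an event after randomisation that may depend on arm and can itself introduce bias.
4. As a secondary clarification, say in section 2.6 that the investigator who receives and files the allocation is not the person who rates outcomes, and that raters and statisticians cannot open the filed record.

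The cost is a few sentences in the protocol and the operating procedures, plus a short log. Sample size, visits and treatment are unaffected.

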### 2.8. Intervention

The intervention schedules for each group are shown in Tables 1 and 2.

### 2.9. Acupuncture Procedure

This study will be conducted based on the Revised Standards for Reporting Interventions in Clinical Trials of Acupuncture (STRICTA) 2010 checklist (Table 3) [12]. Acupuncture will be performed by a KMD who had graduated from a college of Korean medicine with a 6-year course and had been certified by the Korean Ministry of Health and Welfare. With at least 2 years of clinical experience, a KMD who performs all the acupuncture sessions will perform more than 10 hours of training and prior practice. This is a procedure to provide standardized acupuncture sessions consistently according to the prescribed manual of the standard operation procedure (SOP).

*(1) Verum Acupuncture (VA) Group*. The VA session will be conducted twice a week for 4 weeks, and the visit window period will be ±5 days relative to the scheduled date. Participants in the VA group will undergo acupuncture at six acupoints. PC6, LI11, and ST36 will be treated on both sides. GB41, ST43, and LI3 will be treated on only one side—the left side for men and the right side for women. In principle, acupuncture needles will be inserted vertically into all acupoints, and the insertion depth will range from 5 mm to 30 mm, depending on the acupoint location. Acupuncture needles will remain in place for 15 minutes. All acupuncture needles used for participants in the VA group will be disposable sterile stainless steel needles (0.25 × 40 mm; Dongbang Acupuncture Inc., Bundang, Seongnam, Korea). All acupuncture treatments will start after the participants take a 5-minute break upon their arrival.

*(2) Sham Acupuncture (SA) Group*. Sham acupuncture will be conducted twice a week for 4 weeks, and the visit window period will be ±5 days relative to the scheduled date. The SA body sites and depths of acupuncture will differ from those in the VA group. The SA locations will be as follows: 1–2 cm proximal to and 1 cm in the ulnar direction away from PC6 on both sides1 cm proximal to and 1 cm in the ulnar direction away from LI11 on both sides1 cm proximal to and 1 cm in the fibular direction away from ST36 on both sides.

There is no depth standard for SA because SA only involves skin stimulation and not penetration. Sham needles will remain in place for 15 minutes. Park Sham Needles and nonpenetrating sham devices (Park Sham Acupuncture Needles, AcuPrime Co., Ltd., Exeter, UK) will be used for all SA sessions. All sessions will start after the participants take a 5-minute break upon their arrival.

